### Who will take informed consent? {26a}

Study counselors will obtain written informed consent from potential trial participants in person. After discussing study procedures, risk, and benefits in the local language (Marathi or Hindi), the study counselor will test the individual’s understanding. Individuals will be given time to ask questions, reflect, and discuss with family before being invited to provide consent. Eligible index patients will be consented at end of treatment completion to participate for 18 months. HHCs will be consented at the first home visit. For HHCs who are < 18 years or individuals unable to consent for themselves, informed consent will be sought from a legal guardian/representative and additionally, per national guidelines, oral or written assent will be sought from minors.

### Additional consent provisions for collection and use of participant data and biological specimens {26b}

N/A. Biological specimens will not be stored.

### Interventions

#### Explanation for the choice of comparators {6b}

In order to provide evidence for an effective and scalable strategy for detecting recurrent TB among index patients and new cases among HHCs, we will compare two ACF strategies: (i) ACF by home-based symptom screen (HACF) and sputum collection for symptomatic HHCs and (ii) ACF by telephonic symptom screen (TACF) followed by home-based sputum collection for symptomatic HHCs.

#### Intervention description {11a}

In both arms, ACF will be conducted by existing NTEP HCWs at 6 and 12 months after the index patient completes TB treatment. Based on the WHO and Government of India guidelines, the HCW will screen for any symptom of TB, including cough for ≥ 2 weeks, hemoptysis, fever, night sweats, weight loss, or lymph node swelling to screen for extrapulmonary TB [24, 56]. For participants with any symptom of TB, sputum specimens will be collected outside the home in the open air. As per routine programmatic conditions, sputa will undergo Xpert testing (or available microbiologic testing) and results will be returned to the patient.

#### Criteria for discontinuing or modifying allocated interventions {11b}

Participants may withdraw from the study at any time due to personal reasons. In such cases, the participant’s record while in the study will be maintained along with a progress note describing reason for withdrawal. A participant’s allocated arm may not be modified at any time during the study.

#### Strategies to improve adherence to interventions {11c}

To improve adherence to the intervention procedures, HCWs at the participating TUs will be trained in how and when to conduct HACF and TACF. Refresher trainings will be offered periodically. Before each scheduled follow-up, the study staff will provide reminders to NTEP HCWs, and the number of reminders will be tracked. Challenges faced by HCWs will be documented in follow-up logs and regularly assessed to improve strategies. An internal monitor will review procedures on an annual basis, including assessing adherence to the intervention procedures.

#### Relevant concomitant care permitted or prohibited during the trial {11d}

Participants may not be enrolled in another clinical study involving follow-up time points that conflict with TB Aftermath. However, clinical care may be sought at the participant’s discretion during the study period. Participants who report symptoms suggestive of TB disease will be referred to the TU for evaluation. Likewise, asymptomatic HHCs who are identified as potentially eligible for TPT per NTEP guidelines but who have yet to access services will be referred for further evaluation. Index patients newly diagnosed with diabetes at entry, and any participant with lung impairment will also be referred for appropriate care.

#### Provisions for post-trial care {30}

N/A. There is no more than minimal risk to participants associated with study procedures. Thus, post-trial care will not be required.

### Outcomes {12}

#### Primary outcome

The rate per 100 person-years of people diagnosed with new or recurrent TB by study arm, within 12 months following index TB patient’s treatment completion date. TB disease will be diagnosed as microbiologically confirmed (positive acid fast bacilli smear or positive Xpert® MTB/RIF assays or positive culture) or clinically diagnosed (initiated on TB treatment with no microbiological confirmation) [57]. Primary analyses will be based on microbiologically confirmed TB cases among index patients (recurrent TB) or HHCs (new TB), and all analyses will be repeated including clinically diagnosed TB.

#### Secondary outcome

The secondary outcome will be proportion of eligible HHCs < 6 years of age, by study arm, initiated on TPT after ruling out active TB disease. NTEP guidelines include initiation of TPT in children < 6 years of age who are contacts of a patient with TB. At enrolment, participants will report names of HHCs < 6 years of age and their history of TPT. Children who have not yet initiated TPT will be the denominator and children who initiate TPT following index patient enrolment will be the numerator. We will also measure if proportion initiating TPT differs by study arm.

### Participant timeline {13}

The TB Aftermath schedule of evaluations, including responsible personnel, is described for index patients and HHCs in Table 1.

**Table 1 Tab1:** TB aftermath schedule of evaluations

Activity/evaluation	Time point				Administration	
	Entry	+M6	+M12	+M18 (Mop-up)	NTEP HCW	Study staff
**Index patients**						
Informed consent, enrolment and randomization	X					X
Socio-demographic and clinical questionnaires	X			X		X
Household geo-coding	X					X
Biomass fuel, smoking and alcohol exposure questionnaires	X			X		X
Point-of-care HbA1c test	X					X
Lung health assessments	X	X^a^	X^a^	X		X
Modified WHO survey for TB patient costs	X	X		X		X
TB symptom questionnaire	X	X	X	X	X	
TB event questionnaire		Any time TB case is identified				X
**Household contacts**						
Informed consent and enrolment^b^		X	X	X		X
Clinical questionnaire		X^a^		X		X
Lung health assessments		X^a^		X^a^		X
TB symptom questionnaire		X	X	X	X	
TB event questionnaire		Any time TB case is identified				X

^a^Only among HACF arm participants

^b^Study data will not be collected directly from HHCs unless a home visit is conducted and they are consented

*Abbreviations*: *TB* tuberculosis, *WHO* World Health Organization, *HACF* home-based active case finding

The TB Aftermath study flow diagram is depicted in Fig. 1.

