## Data collection and management

### Plans for assessment and collection of outcomes {18a}

#### Objective 1: data collection

##### HACF arm

The NTEP HCW will visit participant homes at 6 and 12 months post-treatment completion to screen the index patient and HHCs for TB. All HH members who screen positive will have a spot sputum taken at home for microbiological testing at the TU.

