##### TACF arm

The NTEP HCW will screen the index patient for TB via telephone calls at 6 and 12 months post-treatment completion; the index patient will also be asked about TB symptoms among HHCs. If TB is suspected among any HH members, a home visit will be conducted and spot sputum specimens will be collected for microbiological testing at the TU.

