##### “Mop-up” campaign

To determine total number of TB diagnoses across HHs in both arms, three strategies will be undertaken. First, all index patient names will be periodically cross-matched with the NTEP registry. Second, on all calls and at all home visits, participants will be asked if there were any TB diagnoses in the period since the last call/visit and when reported will be verified with the NTEP. Third, all HHs in both arms will have an 18-month home visit to screen all HH members for active TB and to survey them for history of TB. We will use the “mop-up” campaign data combined with the registry match data to account for all TB cases occurring during the study period. This will allow for more accurate comparisons between arms and to calculate proportion of overall recurrent and HH TB cases that were captured by our ACF strategies during the study period. In addition, we will compare timing of TB diagnoses between arms, as well as timing of TB detected by our ACF strategies vs. otherwise.

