##### Exposures of interest

*Biomass fuel:* HH biomass fuel use will be assessed using self-reported questionnaires previously validated in our setting [60, 61].
*Smoking:* We will measure exposure to tobacco smoke, nicotine dependence based on the Fagerström Test for Nicotine Dependence, and heaviness of smoking among participants at entry [62].
*Alcohol:* We will measure alcohol use in adult (>= 18 years) participants at entry using the Alcohol Use Disorders Identification Test (AUDIT), which has been validated in India [63].
*Point-of-care HbA1c*: To identify diabetes, defined as HbA1c ≥6.5%, we will measure HbA1c among participants at entry using advanced fluorescent immunoassay technology (Standard F200, SD Biosensor, Republic of Korea). This point-of-care HbA1c test has been validated and approved by Indian regulatory authorities.
*HH socio-economic status:* Participants will describe their type of residence, the number of occupants, type of employment of employed individuals, and monthly HH income.

Visited HHs in both arms will be geocoded using android devises via Redcap during home visits. HHs not visited in the TACF arm will be geocoded during the “mop-up” visit. The residential location will be further characterized by collecting HH-level data such as: predominant housing type, sanitation and infrastructure, transportation access, and distance to closest TU.

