## Statistical methods

### Statistical methods for primary and secondary outcomes {20a}

The primary analysis will be intention-to-treat, which will include all enrolled participants who have completed TB treatment and their household contacts. The primary endpoint is rate of TB disease detected by study arm, which includes recurrent TB among index cases and new TB among HHCs including children. To assess non-inferiority of TACF, compared to HACF, we will estimate a 95% confidence interval around the difference between the observed TB cases diagnosed between arms and establish non-inferiority if the upper bound of this estimate is less than 3 per 100 person-years, the non-inferiority margin. We will analyze impact of key risk factors for TB disease (tobacco smoking, biomass fuel use, alcohol use, diabetes, respiratory impairment, low socioeconomic status, catastrophic costs) on the development of recurrent TB and new TB among HHCs. We will use mixed-effects Poisson regression with random effects for HH and fixed effects for individual level variables to measure the association of key risk factors with recurrent and new TB disease in the HH. For the secondary outcome, a logistic regression model with mixed effects, to account for HH level clustering, will be used to determine if HACF is independently associated with TPT initiation among children < 6 years of age.

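### Household contacts are enrolled only at a home visit, whose timing and trigger differ by arm; if their person-time follows enrolment, the pooled TACF rate is inflated

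*Protocol article*

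**What the plan says.** **Enrolment of HHCs.** The consent section {26a} states that "HHCs will be consented at the first home visit". Table 1 has no HHC consent at entry, only at months 6, 12 and 18, and its footnote b adds: "Study data will not be collected directly from HHCs unless a home visit is conducted and they are consented".

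**Visits by arm.** For HACF: "The NTEP HCW will visit participant homes at 6 and 12 months post-treatment completion to screen the index patient and HHCs for TB". For TACF the index patient is screened by telephone and asked about symptoms in the household, and: "If TB is suspected among any HH members, a home visit will be conducted". The section on exposures foresees TACF households that are first visited at the month-18 mop-up.

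**Ascertainment.** The mop-up section lists three sources. In the registry match, "all index patient names will be periodically cross-matched with the NTEP registry"; HHC names are not mentioned. Participants are asked about TB diagnoses on every call and visit, and reports are verified with the national programme (NTEP). All households in both arms are visited at month 18, when members are screened and asked about past TB.

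**Analysis.** The primary outcome is one rate per 100 person-years over index patients and HHCs, within 12 months of the index patient's treatment completion. The intention-to-treat set is described in {20a} as one "which will include all enrolled participants who have completed TB treatment and their household contacts". The article does not say when HHC person-time starts, or whether HHCs first enrolled at month 18 count.

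**The concern.** Randomisation balances index patients and the households they live in. It does not balance a set of contacts assembled later by a process that depends on the arm. In HACF every household has a routine chance of HHC enrolment at months 6, 12 and 18. In TACF a household without suspected TB has one, at month 18, which lies outside the 12-month window. Earlier TACF enrolment is triggered by suspected TB, so HHCs enrolled early come from households with a raised chance of a case. A household lost before month 18 may already have supplied HHCs in HACF and usually has supplied none in TACF.

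The outcome pools two groups with planned rates of 12 and 1 per 100 person-years. Removing HHC person-time from one arm raises that arm's pooled rate even when detection is identical. More detection is the better result here, so fewer HHCs in TACF would make it look closer to HACF, or better. A false finding of non-inferiority is at stake.

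**Working it through.** **Inputs from the article (Sample size {14}).** Rates of 12 (index) and 1 (HHC) per 100 person-years; two HHCs per index patient; 538 index patients per arm; 10% loss; margin 3. HHC share of planned participants: 2152/3228 = 2/3. The article states no pooled rate. Its 80% power is a separate matter and is not used below.

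**Assumptions (no values in the article).** Each scheduled home visit succeeds with probability q, independently. HACF has three chances and TACF one. HHCs who are reached get person-time for the whole 12-month window, and those not reached get none. The difference is HACF minus TACF; {20a} does not state the direction.

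**1. Pooled rate with k HHCs per index patient and equal true detection.**
Rate(k) = (12 + k)/(1 + k). At the planned k = 2: 14/3 = 4.67.

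**2. Person-time follows enrolment, month-18 enrolees included.**
HACF: k = 2 × [1 − (1 − q)³]. TACF: k = 2q.

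| q | k HACF | k TACF | Rate HACF | Rate TACF | Spurious TACF advantage | Share of margin |
|---|---|---|---|---|---|---|
| 0.9 | 1.998 | 1.8 | 4.67 | 4.93 | 0.26 | 9% |
| 0.8 | 1.984 | 1.6 | 4.69 | 5.23 | 0.54 | 18% |
| 0.7 | 1.946 | 1.4 | 4.73 | 5.58 | 0.85 | 28% |

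If HACF reach at q = 0.8 is rounded up to k = 2, the advantage is 5.23 − 4.67 = 0.56.

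**3. Effect on the error rate at q = 0.8.** Put TACF truly at the margin: full-household rates of 4.67 and 1.67, a detection ratio of 5/14. The observed TACF rate is then 5.23 × 5/14 = 1.87, and the difference is 4.69 − 1.87 = 2.82 instead of 3. Person-years are 484.2 × 2.984 = 1444.9 and 484.2 × 2.6 = 1258.9 (484.2 = 538 × 0.9). The standard error is √(0.0469/1444.9 + 0.0187/1258.9) = 0.69 per 100. The chance of declaring non-inferiority is Φ((3 − 2.82)/0.69 − 1.96) ≈ 4.5%, against the nominal 2.5%. This ignores clustering within households.

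**4. Only HHCs enrolled by month 12 count.** Let a share f of TACF households contribute HHCs, and all HACF households. At f = 0.5 the TACF rate is 13/2 = 6.50, an advantage of 1.83. At f = 0.25 it is 12.5/1.5 = 8.33, an advantage of 3.67, which exceeds the margin.

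**5. All household members count in both arms.** With complete ascertainment both rates are 4.67 and the bias is zero. If a share m of TACF HHC cases is missed, the TACF rate is (12 + 2(1 − m))/3. It falls by 0.17 at m = 0.25, by 0.33 at m = 0.5 and by 0.67 at m = 1, which works against non-inferiority.

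**6. Perfectly correlated visit failure.** If a household that fails one visit fails all of them, both arms reach the same share and step 2 gives zero.

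**The case against.** A reader might infer that nothing about HHCs is known in TACF before a home visit. The article does not support that. Footnote b limits data collected directly from HHCs, while symptoms and diagnoses are also reported by telephone, and reported diagnoses are verified with the NTEP.

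A reader might also infer that the plan is biased towards non-inferiority as it stands. That does not follow either. The outcome window is anchored to the index patient's treatment completion, and the analysis set can be read as including all contacts. The month-18 visit is meant to make case counts comparable between arms. The sample-size section plans two HHCs per index patient across all 1076, which sits poorly with excluding month-18 enrolees, so step 4 is the less likely reading. Missed TACF cases push the other way. Part of any lower HHC detection by telephone is the effect under study, and the early TACF visit is triggered by suspected TB, not by the diagnosed outcome.

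Person-time rules are often left to an analysis plan, and one may exist here. These points limit the size and direction of the concern. They do not remove it: the enrolment rule is fixed in this article, it differs by arm, and a month-18 visit cannot recover contacts in households already lost. An intention-to-treat label does not protect a group formed after randomisation.

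**Conclusion.** The point holds in conditional form. HHC enrolment is post-randomisation and arm-dependent and, in TACF before month 18, is triggered by suspected TB; no registry match is stated for HHCs. If HHC person-time follows enrolment, the crude pooled TACF rate is inflated by about 0.26 to 0.85 per 100 person-years for independent visit success of 90% to 70%, and by more if month-18 enrolees are excluded. If every household member counts from a common date, the bias is zero, or at most 0.67 against non-inferiority. The range rests on the planning rates of 12 and 1, on assumed visit success and on independent failures. Larger figures, such as two HHCs per index patient in HACF against one in TACF (an advantage of 1.83), lie outside that range of visit success and need the month-12 cut-off or a much lower reach. Because the rule governs two thirds of the planned denominator of the primary outcome, it should be settled before arms are compared.

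**What to change.** 1. Record a household count from the index patient at entry, before the envelope is opened, with a list of members where consent rules allow. The article already collects part of this: "Participants will describe their type of residence, the number of occupants", and names of children under 6 are taken at enrolment. For households already enrolled, use the recorded number of occupants.
2. Start HHC person-time at the same index-anchored date in both arms, for all counted members, whether or when a visit takes place.
3. Estimate the arm difference stratified by index patient and HHC, or report the two rates separately beside the pooled rate, so that the HHC mix cannot drive the result.
4. Extend the NTEP registry match to HHCs in both arms where consent allows.

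The cost is one more item on the entry form, extra name matching and a few sentences of analysis text. The main difficulty is the HHC consent rule: counting person-time for members who were never visited must be reconciled with {26a} and footnote b. A count without names needs less than a list, but it leaves cases in unvisited homes dependent on the index patient's report.

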**Fig. 1 Fig1:**
[figure not shown]
TB Aftermath study flow diagram. TB, tuberculosis; HACF, home-based active case finding; TACF, telephonic active case finding; HHC, household contact; TU, TB unit

### Sample size {14}

The sample size for index patients (*n* = 1076) includes 538 in the HACF arm and 538 in the TACF arm (1:1 ratio). On average, we will enroll two HHCs per index patient (*n* = 2152). The total estimated sample size for index patients and HHCs is 3228 individuals.

Data from relevant studies suggest that 10–13% of index patients will develop recurrent TB in each arm [21, 22] and an additional 1–2% of HHCs will develop TB during the study period [58]. Assuming a rate of 12 TB cases per 100 person-years among index patients and 1 TB case per 100 person-years among HHCs, we are powered at 80% to determine that the TACF arm is non-inferior to the HACF arm with a non-inferiority interval of 3 per 100 person-years and a sample size of 1076 index patients and two HHCs per index patient (*n* = 2152). This sample size for the primary outcome is adjusted for 10% projected losses to follow-up. For the secondary outcome, we anticipate that 10% (215/2152) of HHCs will be children < 6 years of age. Data from Pune suggest that approximately 30% of child contacts will have been screened for TB and either initiated on TB therapy or TPT [59]. Thus, we anticipate 70 eligible children in each study arm and hypothesize > 60% to be screened and initiated on TB therapy or TPT in the HACF arm and less than 20% in the TACF arm. We will have at least 90% power to see a difference of 60% vs 20% and 80% power to see a difference of 50% vs 25%.

For objective 2, we will conduct a total of 40 in-depth interviews with index patients (20 with and 20 without recurrent TB) and one HHC for each patient (40 total). We will also interview 20 HCWs to achieve a total sample size of 100. We will use purposive sampling to obtain a maximum variation sample by study arm, as well as gender and age group for index patients, HHCs, and a range of HCW types and levels.

### Recruitment {15}

On a monthly basis, study staff will review NTEP registers to identify all potentially eligible participants nearing the end of their TB treatment at participating TUs. Patients for whom treatment was extended will also be tracked. All potential trial participants will be contacted and screened for enrolment with 60 days of treatment completion. For both index TB cases and HHCs who do not agree to participate, reasons will be documented and discussed by study staff. Accrual reports will be reviewed regularly and additional TUs will be added if required to achieve target sample size.

### Assignment of interventions: allocation

#### Sequence generation {16a}

Trial randomization will be computer-generated, using permuted blocks of equal size with balancing by participating TU.

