#### Trial design {8}

TB Aftermath is a hybrid type I effectiveness-implementation non-inferiority trial with individual randomization. A hybrid type I study is defined by Curran et al. as “testing a clinical intervention while gathering information on its delivery during the effectiveness trial and/or on its potential for implementation in a real-word situation.” [55] The participant allocation ratio between the HACF arm and the TACF arm is 1:1.

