## Methods: participants, interventions, and outcomes

### Study setting {9}

The study will be conducted in three rural and three urban TB Units (TUs) of the NTEP in Pune district, Maharashtra, India. Each of the six participating TUs has the capacity to diagnose TB, initiate treatment, monitor TB treatment outcomes, and serve as directly observed therapy (DOT) centers. Each TU serves a population of approximately 300,000 to 500,000 people. Current responsibilities of existing TU HCWs include diagnosing TB suspects, linking newly diagnosed patients to TB care, visiting HHs within 7 days of index patient treatment initiation, screening HHCs for TB symptoms, referring potentially eligible HHCs for TPT, providing counseling on infection control, ensuring treatment adherence, and finding patients that are lost-to-follow-up. These responsibilities may be distributed among several positions. Urban TUs are usually staffed by a senior TB treatment supervisor (STS), senior TB laboratory supervisor (STLS), lab technician, and a TB home visitor, whereas rural TUs are only staffed by STS and STLS. For this trial, the role of selected NTEP HCWs will be extended to include additional follow-up on patients and HHs beyond treatment.

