#### Concealment mechanism {16b}

The computer-generated allocation (indicating HACF or TACF arm) will be blindly placed in sealed envelopes by data managers. Envelopes will be labeled with the randomization number and stored in numeric order at the TU. After the participant provides informed consent, study counselors will select the next sealed envelope.

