### Assignment of interventions: blinding

#### Who will be blinded {17a}

This is an open-label trial in which both the participants and study staff will be aware of intervention arm after randomization. However, in an effort to reduce potential bias, principal investigators (PIs) and the co-investigators who will be analyzing results will be blinded as to intervention arm.

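### Equal-size permuted blocks within each TB unit, with on-site sequential envelopes opened by the consenting counselors in an open-label trial, make some allocations predictable; hidden varying block sizes would remove most of the certain predictions.

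*Protocol article*

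**What the plan says.** All references are to the protocol article.

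- **Scheme.** Sequence generation {16a} specifies "permuted blocks of equal size with balancing by participating TU". Trial design {8} adds: "The participant allocation ratio between the HACF arm and the TACF arm is 1:1". No block size is stated. Nothing says that sizes vary or are withheld from counselors.
- **Envelopes.** Concealment mechanism {16b}: "Envelopes will be labeled with the randomization number and stored in numeric order at the TU", and "After the participant provides informed consent, study counselors will select the next sealed envelope". Implementation {16c} confirms that consent comes before opening.
- **Who recruits.** Under Who will take informed consent? {26a}: "Study counselors will obtain written informed consent from potential trial participants in person". The same role therefore takes consent and opens the envelope.
- **Blinding.** The blinding section, item {17a}, reads: "This is an open-label trial in which both the participants and study staff will be aware of intervention arm after randomization". Only the principal investigators and the co-investigators doing the analysis are to be blinded.
- **Recruitment.** Under Recruitment {15}, staff review the program registers monthly, all potential participants are to be contacted and screened, and reasons for refusal are recorded. Eligibility criteria {10} allow enrolment up to 60 days from treatment completion.

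**The concern.** A sealed envelope hides the current allocation, but in an open-label trial it cannot hide what earlier allocations imply. With one fixed block size per TU, someone who remembers the sequence can work out where each block ends, and late in a block the next arm may be certain.

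The person able to do this is the one who approaches and consents the next patient. There could be reasons to prefer an arm. Table 1 gives study staff additional month 6 and month 12 lung assessments in the home-based arm only, and patients differ in distance from the TU and in how easily they are reached by telephone.

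If such patients were timed toward one arm, the arms could differ in recurrence risk and in the chance that TB is found. The article itself links socio-economic status to recurrence. The rate difference is judged against a margin of 3 per 100 person-years. Intention-to-treat does not correct selection that happens before randomization, and blinding the analysts comes too late to affect it.

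**Working it through.** The article gives no block size and no predictability figure, so there is no stated number to reproduce.

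**Inputs.** 1:1 allocation ({8}); one block size, balanced by TU ({16a}); six TUs ({9}); 1076 index patients ({14}). Assumptions: even enrolment, so 1076 / 6 ≈ 179 per TU; block sizes 4, 6 and 8 as typical, with 2 and 12 as outer values.

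**Step 1: certain allocations when the size is known.** In a block of size 2m with m per arm, every position after one arm is used up is certain. The expected share is 1/(m+1). Check for size 4: up to swapping arms the sequences are AABB, ABAB and ABBA, with 2, 1 and 1 certain positions. The mean is 4/3, and (4/3)/4 = 1/3.

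**Step 2: best guess when the size is known.** Always naming the under-represented arm is right in a share [m + (2^(2m)/C(2m,m) − 1)/2] / (2m). For m = 2: [2 + (16/6 − 1)/2]/4 = 0.708. For m = 3: [3 + (64/20 − 1)/2]/6 = 0.683. For m = 4: [4 + (256/70 − 1)/2]/8 = 0.666.

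**Step 3: size not known.** A simulated observer records every allocation at one TU (179 allocations, 300 runs per size). The observer starts with equal weight on sizes 2, 4, 6, 8 and 10 and updates by Bayes' rule. A prediction counts if it is more than 99% sure.

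| Fixed block size | Certain, size known | Of 1076 | Best guess correct | Median allocations to identify size (95% posterior) | Predictable, size learned |
|---|---|---|---|---|---|
| 4 | 33% | 359 | 71% | 36 | 26% |
| 6 | 25% | 269 | 68% | 32 | 21% |
| 8 | 20% | 215 | 67% | 20 | 18% |

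Over the wider range, the certain share with known size runs from 50% (size 2, 538 patients) to 14% (size 12, 154 patients).

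**Step 4: hidden, randomly varying sizes.** The observer knows the set of sizes but not the draws (exact Bayesian filter, 179 allocations, 300 runs).

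| Mix | Certain | Best guess correct |
|---|---|---|
| 4/6 | 5.3% | 69% |
| 2/4/6 | 4.0% | 70% |
| 4/6/8 | 2.5% | 68% |
| 4/6/8/10 | 1.2% | 67% |

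Certainty falls by a factor of 8 to 13 for the 4/6/8 mix (20/2.5 to 33/2.5). Best-guess accuracy improves on fixed 4 by about 3 points and does not improve on fixed 6 or 8.

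**Step 5: what a prediction could be used for.** Contacting all listed patients means a counselor is not free to pick from a pool. Consent before opening means a patient cannot be turned away once the arm is seen. Two things remain: the order and timing of approach within the 60 days, and how hard a patient is encouraged to join.

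**The case against.** - **The shares in Step 1 are ceilings.** This stands. They require the size to be known from the first patient and one person to see the whole sequence at a TU. The article says neither, nor how many counselors serve a TU. Learning the size lowers the shares to 26%, 21% and 18%, and that still assumes perfect record-keeping.
- **Recruitment is register-based and complete by design.** This stands in part. It narrows the opening to order, timing and persuasion but does not close it.
- **Motive is conjecture.** Screening in both arms carries minimal risk and is done by program health workers, not counselors. Registry matching of index patients and the 18-month home visit in both arms soften differences in traceability. This is fair, and no size or direction of bias can be given. The home-based-only lung assessments do fall to study staff, so a preference is not far-fetched.
- **Poor concealment is not the cause of the guessing advantage.** Correct. A reader might infer that full concealment would bring best-guess accuracy down to 50%. It would not: 50% belongs to unblocked randomization. Perfectly concealed blocks in an open-label trial give the same 71%, 68% and 67%, because the guess uses past allocations.
- **Equal size might loosely mean equal arm numbers within a block.** Possible, but one common block size is the natural reading and nothing in the article says that sizes vary.
- **It is late to change.** Recruitment ran from January 29, 2021 to about February 1, 2023 (733 days). The article appeared on August 5, 2022, day 553, about 75% of the way through. The change helps only those not yet randomized.

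**Conclusion.** The point holds as a weakness in a stated design rule. Equal-size blocks by TU, combined with on-site sequential envelopes, open-label allocation and one role that both consents and opens, let a share of allocations be known in advance. For sizes 4 to 8 that share is at most 20% to 33%, or about 18% to 26% if the size must be learned. This rests on an undisclosed block size, one attentive observer per TU and even enrolment over six TUs. Selection bias is possible through the order and timing of approach.

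A reader might go further and conclude that allocations were steered or that the comparison is biased. The article does not support that: it shows an opportunity that its own recruitment rules restrict, and no evidence of use. Nor does it support saying that the current envelope is unprotected. Severity is minor to moderate, and the remedy is a cheap improvement.

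**What to change.** **Patients not yet randomized.** Regenerate the unused part of each TU's list with randomly varying block sizes, for example 4, 6 and 8, and withhold the sizes from TU staff. Apply the same rule to any TU added later to reach the target. State in the protocol that sizes vary and are concealed, without listing them where counselors can read them. This cuts certain predictions to about 2.5%. It does not remove the general guessing advantage, which stays near 68%. If sizes already vary or are withheld, one clarifying sentence would largely settle the point.

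**Patients already randomized.** Compare entry characteristics by arm and by position in the block, looking in particular at allocations that earlier ones in the block had made certain. This needs only the allocation list and entry data and can be done after recruitment closes. It can reveal selection only on measured characteristics.

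**Cost.** New lists, re-filled envelopes and slightly looser balance within a TU. The largest imbalance within a TU at any moment is half the largest block, so 4 with the 4/6/8 mix against 2 with fixed blocks of 4, plus any block left unfinished at the switch.
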